#### 1.6.2.2. Assessment of (Non-)Attendance at the BETER clinics

Preliminary data from a small study in a few BETER clinics show that 60-70% of the HL survivors who were invited attended the BETER clinic. We found that especially survivors who were no longer under medical surveillance at the BETER centre were less likely to attend. The most common reasons not to attend were having already been diagnosed with adverse events elsewhere and unwillingness to attend (e.g. due to emotional burden). A possible reason for declining may be that survivors do not want to become a lifelong patient instead of a cancer survivor. Also, financial considerations may play a role, as Dutch healthcare insurance includes a mandatory deductible sum of 385 euros as of 2016, which not everyone is able or willing to pay. More detailed evaluation of (non-)attendance in more BETER clinics may reveal the need for additional implementation measures to improve the uptake of the programme. Survivors who have declined the invitation to visit a BETER clinic will also be asked to fill in the BETER questionnaire. The BETER questionnaire contains items that assess a survivor's health care use and screening history: what, when, how and where (at which hospital/GP) is screened for. This will help us to get a better picture of the patient characteristics and current health issues of the non-attending survivors. It will also provide information on which part of these survivors is already partly screened according to (some of) the BETER guidelines. To elucidate possible financial reasons for (non-)attendance, we will infer social economic status from postal code and assess whether it correlates with attendance rate, as financial considerations about the mandatory deductible sum in health care insurance may play a role in declining the invitation.

#### 1.6.2.3. Health Care Use, incl. Screening Practices

Information on the overall health care use (medication, GP visits, hospital visits and hospitalisation) between 2013-2016 and 2021-2024 in the intervention and control groups will be extracted from hospital medical records, the survivors' general practitioners, disease registries and the self-administered BETER questionnaire. It will allow us to compare overall health care use between the intervention and control groups, as well as compare survivors who have accepted and declined to attend the BETER clinic. This will provide more insight into the patient characteristics of those who declined to attend the BETER clinic: e.g. are they not experiencing any health complaints or is their health compromised and are they treated/screened for late treatment effects elsewhere? See also 1.6.2.2.

#### 1.6.2.4. Assessment of Knowledge about Late Adverse Effects and Risk Perception of Late Effects

Despite the fact that in recent years increasing attention has been given to the need for follow-up care, cancer survivors are often unaware of their risk of treatment-related adverse effects, which may delay diagnosis and treatment of these adverse effects (25). In childhood HL survivors it was shown that increased awareness of possible late effects may influence the health

behaviour of cancer survivors and increase participation rates in screening programs (26). This underlines the importance of increasing awareness and knowledge about treatment-related adverse effects in lymphoma survivors. In the proposed project, knowledge about treatment-related adverse effects will be examined with a slightly adapted version of a questionnaire CCSS (25) in both the intervention and control groups. Most items consist of statements covering the wide range of treatment-related adverse effects and the level of risks after HL treatment, including knowledge about the need for screening. Survivors who have declined the invitation to visit a BETER clinic will also be asked to fill in this questionnaire. Survivors in the control group will be asked to fill in this questionnaire before their first BETER visit.

#### 1.6.2.5. Assessment of Distress about Late Effects

Detailed information on late effects could cause increased levels of distress in survivors. We therefore want to assess the effect of BETER survivorship care on worries about treatment-related adverse events and will ask survivors in the intervention and control group to fill in a 6-item questionnaire based on the Cancer Worry Scale (CWS) (27). The scale assesses frequency of concerns about developing treatment-related adverse effects and the impact of these concerns on mood and daily functioning on a 4-point scale. Survivors who have declined the invitation to visit a BETER clinic will also be asked to fill in this questionnaire. Survivors in the control group will be asked to fill in this questionnaire before their first BETER visit.

### 1.7. SAMPLE SIZE CALCULATION

#### 1.7.1. Assessing the potential health gains

To assess the potential health gains (in terms of averted DALYs) of BETER survivorship care, a model was constructed in which the burden of disease accumulated during 5-year follow-up (note: the follow-up in the proposed study is expected to be longer) was calculated for the intervention group, screened at a BETER clinic, and the control group. The model includes cumulative incidence of the late adverse events after treatment under study: (risk factors of) CVD, breast cancer, hypothyroidism and overwhelming post-splenectomy infections due functional asplenia. The risk of these conditions is substantially increased: see 1.3.1. BETER Screening Recommendations for Late Adverse Effects after Lymphoma Treatment. The impact of treating the CVD risk factors high blood pressure and hypercholesterolemia on developing CVD and death from CVD was inferred from risk reduction tables published by the Dutch Society of General Practitioners ([www.nhg.org/sites/default/files/content/nhg\\_org/uploads/cvrm\\_protoc\\_bijlagen\\_web\\_13.pdf](http://www.nhg.org/sites/default/files/content/nhg_org/uploads/cvrm_protoc_bijlagen_web_13.pdf)). Disability weights for CVD were extracted from the Global and Dutch Burden of Disease studies (19,21). The number of DALYs averted by breast cancer screening was based on a cost-effectiveness study on breast cancer interventions (28). Based on this model, we estimated that the average HL survivor of 52 years of age, who is not screened for late adverse treatment events, acquires 1.18 DALYs in the next 5 years (1.12 for breast cancer + CVD; 0.01 for hypothyroidism; 0.04 for functional asplenia), as opposed to 0.56 DALYs for a survivor screened at a BETER clinic (0.55 for breast cancer + CVD; 0.00 for hypothyroidism; 0.00 for functional asplenia). [Of note, the numbers do not add up due to rounding.] We therefore assume that, at patient level, screening at the BETER clinics averts on average 0.62 DALYs per survivor in a 5-year period. In the 1.8. DATA-ANALYSIS section we describe that we will perform an 'intention to screen' analysis, assessing the impact of BETER survivorship care including survivors who choose not to attend. Preliminary data from a small study in a few BETER clinics showed an attendance rate of 60-70%. When we take an attendance rate of 65% into account, the expected difference between the intervention and the control group is 0.40 DALY: 0.78 DALYs in the intervention group (65% of 0.56 DALYs + 35% of 1.18 DALYs) and 1.18 DALYs in the control group.

#### 1.7.2. Sample size calculation

In the 'intention to screen' analysis, we expect a 5-year accumulation of 0.78 DALYs in the intervention group and 1.18 DALYs in the control group. With a 2-sided significance level of 0.05 and 80% power to detect a difference of 0.20 standard deviation (small effect size) and larger, we need 393 patients in each study arm. When we take 15% loss to follow-up and incomplete data into account, we need 452 patients in each study arm.

#### 1.7.3. Effect size for other analyses

Now that we have powered for the 'intention to screen' analysis, what are the effect sizes we can detect in other analyses? For the patient level analysis we anticipate only 7% incomplete data (as these survivors all are or have been attending a BETER clinic). With an attendance rate of 65% we anticipate 274 survivors at patient level analysis in each arm (65% of 452/1.07). This allows us to detect a difference of at least 0.24 standard deviation (small effect size) with an expected difference of 0.62 DALYs between intervention and control group, a 2-sided significance level of 0.05 and 80% power.

For important sub-analyses, comparing for example the yield/incidence of the different CVD outcomes or subgroups according to age (above/below 50 years) or sex, the proposed sample size provides 80% power to detect medium effect sizes (0.50 standard deviation). These analyses are relevant to provide information on the effectiveness of specific guidelines, and because guidelines are different for males and females (regarding breast cancer screening) and different age groups.

### 1.8. DATA-ANALYSIS

#### 1.8.1. Intention to screen analysis

To assess the impact of BETER survivorship care on the centres' eligible lymphoma population, the outcome parameters will be compared between the first 450 survivors who were invited to a BETER clinic that started in 2013-2014 and 450 matched survivors who were treated for lymphoma at BETER centres that does not start a clinic until 2021-2024. Reasons why participating centres did not start a BETER clinic before 2021 are of logistic nature involving identification and tracing of patients and setting up the infrastructure, especially the availability of an interested cardiologist and a nurse-practitioner; factors very unlikely to be associated with treatment-specific risks of late effects and our study outcomes. Centres starting an early BETER clinic included both University Medical Centres and large peripheral hospitals. This allows us to use an instrumental variable analysis with the variable 'treated for lymphoma at a centre with a BETER clinic that started in 2013-2014' (y/n) as instrumental variable. We hereby mimic randomization and minimize the risk of bias in this observational study. The variable 'treated for lymphoma at a centre with a BETER clinic that started in 2013-2014' is strongly associated with the likelihood of

receiving the intervention (65% vs. 0-5% for clinics that started in 2013-2014 and 2021-2024 respectively), but not associated with any prognostic factor or with the outcome (other than through the intervention). The attendance rates are based on preliminary data from a small study in a few BETER clinics which showed that the attendance rate was 60-70% and that survivors only rarely visited a BETER centre not connected to their original lymphoma treatment centre. Individual matching of control group participants to the intervention group on relevant treatment characteristics will control for any differences in lymphoma treatment between centres.

When we select the matched comparison group eligible for BETER care in 2013-2016, we do not yet know whether they will attend the BETER clinic when invited in 2021-2024; therefore, in a truly unbiased analysis, attendance should not be an eligibility criterion in the intervention group as well. Our intention-to-screen analysis is therefore the most valid approach to evaluation of the cost-effectiveness of BETER survivorship care.

#### 1.8.2. Patient level analysis

To assess the impact of BETER survivorship care on screened/treated individuals, outcome parameters will be compared between the first 270 survivors who attended a BETER clinic that started in 2013-2014 and matched survivors who are not (yet) screened and were treated for lymphoma at BETER centres that start a clinic in 2021-2024.

On both levels of analysis, multiple linear regression analysis will be used for continuous outcomes (such as DALYs and health care costs) and Poisson or negative binomial regression analysis will be used for count variables (i.e. yield of previously undiagnosed adverse events). The regression analyses will also take the amount of follow-up time into account, thereby correcting for a possible difference in follow-up time in the intervention and control group.

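### The patient-level analysis selects on attendance and its control group is described in two ways; a complier-average (instrumental-variable) estimate should be the main measure of the effect in screened survivors

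*Protocol*

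**What the plan says.** **The comparison.** Section 1.8.2 states that "outcome parameters will be compared between the first 270 survivors who attended a BETER clinic that started in 2013-2014 and matched survivors who are" (still unscreened, at centres whose clinic opens in 2021-2024). It sets no condition on whether those controls later attend.

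**The sizing.** Section 1.7.3 says "we anticipate 274 survivors at patient level analysis in each arm", obtained as 65% of 452/1.07. The attendance rate is thus applied to both arms. Only 7% incomplete data is allowed, on the ground that "as these survivors all are or have been attending a BETER clinic". The stated detectable difference is 0.24 SD.

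**Deaths among controls.** The end of section 1.2.3, and the reply to the funder in 8.5.1, state that matched controls who died before their 2021-2024 invitation are eligible. The reply relies on this to show that mortality can be measured.

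**Who attends.** Section 1.6.2.2 reports that "The most common reasons not to attend were having already been diagnosed with adverse events elsewhere" and unwillingness. It adds that survivors no longer under surveillance at the centre were less likely to come.

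**The plan's own position.** Section 1.8.1 says that in an unbiased analysis "attendance should not be an eligibility criterion in the intervention group as well", and ranks intention to screen as the most valid approach. It also says that the design permits an instrumental-variable analysis, with treatment at an early-clinic centre as instrument (uptake 65% against 0-5%). Section 1.8.2 then names linear and Poisson or negative binomial regression for both levels and gives no instrumental-variable estimator.

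**The concern.** The patient-level analysis is meant to show what BETER care does for people who are actually screened, where the plan expects 0.62 DALY averted over 5 years. Two things stand in the way.

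First, under 1.8.2 only the intervention arm is filtered by attendance. The controls still contain the counterparts of those who would decline. The matching factors in 1.2.3 (sex, age, year and treatment) do not include existing morbidity, so they do not remove this difference.

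Second, under the set implied by 1.7.3, controls must live long enough to attend in 2021-2024. By section 1.6.1.2 a DALY is years of life lost (YLL) plus years lost to disability. A control set made up only of later attenders has no YLL from the follow-up period, whereas an intervention attender can die after the first visit and contribute YLL.

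The estimate in screened survivors would then partly reflect who attends, or who survives to attend. The two sections also cannot both govern one analysis.

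**Working it through.** **1. The plan's figures reproduce.**
- Intention to screen, 0.20 SD, two-sided 0.05, 80% power: n = 2 × (1.960 + 0.842)² / 0.20² gives 393 per arm; 393 × 1.15 = 452.
- Patient level: 0.65 × 452 / 1.07 = 274.6. Detectable difference = 2.802 × √(2/274) = 0.239 SD, stated as 0.24.
- With the 270 of section 1.8.2 it is 0.241 SD, so 270 against 274 is immaterial.
- Expected intervention mean: 0.65 × 0.56 + 0.35 × 1.18 = 0.777; difference 1.18 - 0.777 = 0.403 DALY.

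The arithmetic is sound. The problem is the comparison.

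**2. Section 1.8.2 reading: attenders against controls not selected on attendance.** Let r be the untreated burden of non-attenders divided by that of attenders. The protocol does not give r, so it is an assumption. Both populations are taken to be 65% attender types with an untreated mean of 1.18. The attenders' untreated mean is a = 1.18 / (0.65 + 0.35r), and the spurious effect is 1.18 - a.

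| r (assumed) | a | Spurious effect | Estimate if the true effect is 0.62 |
|---|---|---|---|
| 0.67 | 1.334 | -0.15 | 0.47 |
| 1 | 1.180 | 0 | 0.62 |
| 1.25 | 1.085 | +0.10 | 0.72 |
| 1.5 | 1.004 | +0.18 | 0.80 |
| 2 | 0.874 | +0.31 | 0.93 |

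**3. Section 1.7.3 reading: controls are later attenders.** Let s be the YLL share of control DALYs, also not given and so assumed. If deaths are removed from the controls only, and the surviving controls' disability burden is otherwise unchanged, the control mean is 1.18 × (1 - s). The expected difference is that mean minus 0.56.

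| s (assumed) | Control mean | Difference |
|---|---|---|
| 10% | 1.062 | 0.50 |
| 25% | 0.885 | 0.33 |
| 50% | 0.590 | 0.03 |

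The sign reverses only above about 53% (1 - 0.56/1.18).

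**4. Instrumental-variable estimate on the plan's figures.** Effect in compliers = intention-to-screen difference / uptake difference.
- Uptake 65% against 0%: 0.403 / 0.65 = 0.62.
- Uptake 65% against 5%: the expected difference is 0.62 × 0.60 = 0.372, and 0.372 / 0.60 = 0.62.
- In every row of the first table, with 0% control uptake, this ratio returns the true effect, because it does not depend on r.

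**5. Precision, before clustering, with 393 evaluable per arm.**
- Detectable effect: 0.20 / 0.65 = 0.31 SD, or 0.20 / 0.60 = 0.33 SD. Over uptake of 60-70% against 0-5% the range is 0.29-0.36 SD.
- Reaching 0.24 SD this way would need about 646 (65% against 0%) to 758 (65% against 5%) evaluable per arm.
- The SD of DALYs is not stated. If 0.40 DALY is equated with 0.20 SD, the SD is 2.0 and 0.62 DALY is 0.31 SD. Power is then about 81% (65% against 0%) or 74% (65% against 5%).

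**The case against.** The plan already treats this analysis as secondary in rank. Section 1.7.2 sizes the study on intention to screen alone, and 1.7.3 only asks what other analyses could detect. This stands, and it confines the harm to the estimate in screened survivors.

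A reader might infer that 1.8.2 flatters BETER, because people already diagnosed elsewhere stay away. The documents do not settle that. Section 1.6.2.2 also names unwillingness and absence of surveillance as linked to non-attendance, and 1.6.2.3 leaves open whether decliners are well or unwell.

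A reader might also infer that control YLL is zero and that the effect disappears. But the attender-only control set is deduced from sample-size wording. Equal arms could also come from matching one control per attender, and sections 1.2.3 and 8.5.1 point the other way. A vanishing effect needs an assumed YLL share of about half or more. The 7% justification still fits only an attender set, so the conflict remains.

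Nor do the documents show that no instrumental-variable estimate will be produced. Section 1.8.1 announces one, and naming linear regression does not exclude two-stage least squares. What is established is that the protocol does not attach it to the patient-level question.

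Finally, the match of 0.403/0.65 with 0.62 is circular as evidence, since the plan derived 0.40 from 0.62 and 65%. It shows only that the target quantity is the same. With any uptake among controls, the complier effect is not exactly the effect in everyone screened.

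**Conclusion.** The concern holds in limited form and should be fixed. As written, section 1.8.2 yields an estimate in screened survivors that is open to selection on attendance, and section 1.7.3 sizes a different control set that conflicts with the stated eligibility of controls who died.

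Under 1.8.2 the direction and size of the bias are unknown: about -0.15 to +0.31 DALY against 0.62, for an assumed r of 0.67 to 2. Under the 1.7.3 reading, removing control deaths works against BETER, leaving 0.50, 0.33 or 0.03 DALY at assumed YLL shares of 10%, 25% or 50%.

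It would go too far to conclude that the trial's main result is compromised: this point does not touch the intention-to-screen comparison.

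**What to change.** 1. Reconcile sections 1.7.3 and 1.8.2 to one control definition that keeps controls who died before invitation.
2. Make the main estimate of the effect in screened survivors a complier-average effect from all 450 + 450. Use two-stage least squares with early-clinic centre as instrument, attendance as exposure and the observed uptake difference (planned at 65% against 0-5%) as divisor. Standard errors must allow for few centres: the protocol mentions 5 first clinics (Health care efficiency problem) and 12 hospitals (section 6). Name a corresponding instrumental-variable method for the count outcomes.
3. Replace the statement of 274 per arm and 0.24 SD with a detectable effect of about 0.31-0.33 SD before clustering.
4. Keep attenders against controls only as a labelled supportive analysis.

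The cost is wording and modest programming, with no new data. The interval will be wider, and the estimate rests on the assumption that centre affects outcome only through BETER care, which section 1.8.1 already makes. Intention to screen remains the main analysis.

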#### 1.2. PATIENT (P)

##### 1.2.1. Patient population

The study will be nested in a large nationwide retrospective cohort study of HL survivors treated in 27 Dutch centres between 1965 and 2012 (15,16). This cohort was originally established in the 1980s-1990s to examine the late effects of HL treatment; since then the cohort has been periodically extended with more treatment centres, patients diagnosed in more recent years and with diffuse large B-cell lymphoma (DLBCL) survivors diagnosed between 1989 and 2012. Lymphoma survivors eligible for BETER survivorship care were successfully treated at least 5 years ago for HL or DLBCL at age 15-60 years and are less than 70 years of age at invitation. The patient population in this evaluation study will only consist of HL survivors eligible for BETER survivorship care, as they were the first to be invited to the BETER clinics in 2013-2016 due to their higher risk of late adverse treatment effects compared to DLBCL survivors.

1.2.2. Intervention group: the first 450 HL survivors between 2013 and 2016 who were invited for screening for late adverse treatment effects in the BETER centre where they were originally treated for HL. With attendance rates ranging between 60-70%, around 300 HL survivors in the intervention group are expected to receive screening at the BETER clinics.

1.2.3. Control group: frequency matched group of 450 HL survivors, eligible for BETER screening for late adverse treatment effects in 2013-2016, but not yet invited because the centre where they were originally treated for HL does not start a BETER clinic until 2021-2024. So, the control group will be invited in 2021-2024.

Controls will be matched with the intervention population on the following criteria:

- sex
- age at diagnosis ( $\pm 3$  years)
- year of diagnosis ( $\pm 3$  years)
- lymphoma treatment characteristics associated with increased risk of CVD, breast cancer, hypothyroidism and functional asplenia (see also 1.3.1.). In practice this implies matching on chest radiotherapy (y/n), neck radiotherapy (y/n), spleen radiotherapy (y/n), splenectomy (y/n) and anthracyclines (y/n + doxorubicin  $\approx 300$  mg/m^2 y/n).

Survivors selected as controls should be alive at the time the corresponding survivor in the intervention group was invited to

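### Section 1.8.2 fixes the patient-level group at the first 270 attenders, a number with no derivation that does not match the attenders expected in 1.2.2 and 1.7.3

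*Protocol*

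**What the plan says.** Three sections of the protocol bear on the size of the patient-level group.

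- Section 1.2.2 takes 450 invited survivors and attendance of 60-70%, and concludes that "around 300 HL survivors in the intervention group are expected to receive screening at the BETER clinics".
- Section 1.7.3 sizes the patient-level analysis: "With an attendance rate of 65% we anticipate 274 survivors at patient level analysis in each arm (65% of 452/1.07"). The divisor comes from an allowance stated just before it: "For the patient level analysis we anticipate only 7% incomplete data (as these survivors all are or have been attending a BETER clinic"). From 274 per arm it concludes: "This allows us to detect a difference of at least 0.24 standard deviation (small effect size"). The conditions attached are 80% power, two-sided testing at 5%, and 0.62 DALYs as the anticipated gap between the groups.
- Section 1.8.2 defines the group that will be analysed: "the first 270 survivors who attended a BETER clinic that started in 2013-2014", compared with matched survivors not yet screened.

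Section 1.8.1 uses a parallel phrase for the intention-to-screen analysis, "the first 450 survivors who were invited to a BETER clinic that started in 2013-2014". Section 1.6.1.1 provides for data from every BETER visit to be collected for the intervention group.

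**The concern.** The analysis section turns a number into a selection rule. Taken as written, the group closes at the 270th attender, and nothing is said about those who come after. No section explains why 270 was chosen, and it agrees with neither of the other two counts.

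Two things are at stake, both modest. First, attenders who are already in the cohort and already abstracted would be left out, with no saving and some loss of precision. Second, it is unclear whether 270 counts attenders before or after removal of incomplete records, so a reader cannot tell whether the detectable difference in 1.7.3 applies to the group in 1.8.2. Left open, the choice of which attenders count would be made with the data in hand.

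**Working it through.** **Inputs.** Invited: 450 (1.2.2, 1.8.1), or 452 in the sample size (1.7.2). Attendance: 60-70%, with 65% used for planning (1.2.2, 1.7.3). Incomplete data at patient level: 7% (1.7.3). Two-sided alpha 0.05, power 80%, equal arms, effect in SD units (1.7.3).

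**Formulas (two means, normal approximation).** Detectable difference = (1.960 + 0.8416) × √(2/n). Power at 0.24 SD = Φ(0.24 × √(n/2) − 1.960).

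**Step 1: the plan's own figure.** 0.65 × 452 = 293.8 attenders, and 293.8/1.07 = 274.6, stated as 274. At n = 274 the detectable difference is 2.8016 × √(2/274) = 0.239 SD, and power at 0.24 SD is 80.2% (80.1% with the noncentral t). Section 1.7.3 is reproduced, and its 274 is net of the 7%.

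**Step 2: attenders expected among 450.**
- 60%: 0.60 × 450 = 270
- 65%: 0.65 × 450 = 292.5
- 70%: 0.70 × 450 = 315

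So 270 is exactly the lower limit. A literal stop at 270 omits 0, 22.5 or 45 attenders: 0%, 8% (22.5/292.5) or 14% (45/315).

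**Step 3: two readings of 270.**

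| Reading | Complete per arm | Power at 0.24 SD | Detectable at 80% |
|---|---|---|---|
| 270 is net of incomplete data | 270 | 79.6% | 0.241 SD |
| 270 is before incomplete data | 270/1.07 = 252 | 76.9% | 0.250 SD |

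Taking the 7% as a multiplier instead gives 270 × 0.93 = 251, power 76.7% and 0.250 SD.

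**Step 4: all attenders among the 450.** At 65%, 292.5/1.07 = 273 complete, with power 80.1% and a detectable difference of 0.240 SD. At 70%, 315/1.07 = 294 complete, with power 82.9% and 0.231 SD. At 60% the group is the same 270 attenders as under the cap, so nothing is lost by dropping the cap.

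**Step 5: power for the expected 0.62 DALYs.** The protocol gives no SD for DALYs, so this needs an assumption. With SD 2.0 (0.40/0.20), 0.62 is 0.31 SD and power at 252 per arm is about 93.6%. With SD 2.58 (0.62/0.24), it is 0.24 SD and power is 76.9%.

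**The case against.** The strongest reply is that 270 is simply 274 rounded. The protocol rounds 452 to 450 elsewhere, and the 1.7.3 formula applied to 450 gives 273. On that view 270 is already net, taking 7% off again counts the loss twice, and the stated 0.24 SD at 80% power stands. This is plausible and cannot be ruled out. Against it, the sentence speaks of survivors who attended and says nothing of complete data. The parallel 450 in 1.8.1 is a count before loss, since 1.7.2 reaches its total by inflation: "When we take 15% loss to follow-up and incomplete data into account, we need 452 patients in each study arm". The text does not settle the matter.

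It is also fair to say that 0.24 SD is not a design target. Section 1.7.3 reports what the patient-level analysis can detect once the intention-to-screen analysis has fixed the sample size, and 0.25 instead of 0.24 SD would change little. The figures of about 300 and 274 do not conflict either, since one is before loss and the other after.

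Finally, a reader might infer that the cap biases the comparison by favouring prompt responders. The documents do not support that. They do not say whether first refers to invitation or to visit date, and nothing links speed of attendance to outcome. The larger selection issue, attenders against non-attenders, is acknowledged in 1.8.1 and is the reason given there for preferring intention to screen.

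What survives the objection is that 270 is unexplained and unlabelled, and that as a literal rule it leaves out usable attenders.

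**Conclusion.** The point holds as an inconsistency in how the patient-level group is defined. The count in 1.8.2 does not follow from 1.2.2 or 1.7.3. Read literally, it omits about 22-23 attenders at the planned 65% attendance (0 to 45 over 60-70%) for no gain.

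A reader might go further and conclude that 80% power at 0.24 SD is not met. That follows only if 270 is a count before incomplete data, where power is about 77% and the detectable difference 0.25 SD. If 270 is net, power is 79.6% and the claim in 1.7.3 essentially stands. These figures assume equal arms with the same 7% loss in both. The intention-to-screen analysis, which sets the sample size and which the protocol regards as the most valid, is not affected. This is a small improvement to the plan and not a threat to its main conclusion.

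**What to change.** In 1.8.2, replace the fixed count with all survivors among the 450 invited who attended, together with their matched controls. At 65% attendance this gives about 273 with complete data, which supports 0.24 SD at 80% power. Then make 1.2.2, 1.7.3 and 1.8.2 agree, labelling each number as before or after incomplete data.

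If 270 is kept, state which of the two it is. If it is before incomplete data, restate 1.7.3 as about 252 per arm and 0.25 SD.

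The cost is a sentence in 1.8.2 and matching edits to the counts. On the intervention side no patients or data collection are added, because these survivors are already in the group and their visits are already to be abstracted. Their matched controls can come from the 450 controls already planned.
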